**Methods and design:**

This study compares two acupuncture groups (with or without manipulation) in 292 patients with a history of subjective tinnitus. The trial will be conducted in the Teaching Hospital of Chengdu University of Traditional Chinese Medicine. In the study, the patients will be randomly assigned into two groups according to a computer-generated randomization list and assessed prior to treatment. Then, they will receive 5 daily sessions of 30 minutes each time for 4 consecutive weeks and undergo a 12-week follow-up phase. The administration of acupuncture follows the guidelines for clinical research on acupuncture (WHO Regional Publication, Western Pacific Series Number 15, 1995), and is performed double-blind by physicians well-trained in acupuncture. The measures of outcome include the subjective symptoms scores and quantitative sensations of *De Qi* evaluated by Visual Analog Scales (VAS) and the Chinese version of the ‘modified’ Massachusetts General Hospital Acupuncture Sensation Scale (C-MMASS). Furthermore, adverse events are recorded and analyzed. If any subjects are withdrawn from the trial, intention-to-treat analysis (ITT) and per-protocol (PP) analysis will be performed.

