### Recruitment and randomization procedures

The participants will be recruited through advertisements in local newspapers, hospital websites, and television. Printed recruitment posters will also be posted in the hospital and the university campus. Then, the participants will be randomly assigned to either the manipulation or the non-manipulation group with an assignment ratio of 1:1 according to the random number of allocation sequence generated by computer (using SPSS 19.0 statistical software package, IBM, Chicago, IL, USA). The random allocation numbers are sealed separately in opaque envelopes separately. After the participants have picked-up one of the envelopes, their random numbers and corresponding randomization information, such as the participant’s name in a pinyin format and gender, will be recorded in a random allocation table in duplicate and sealed in an opaque container respectively. The container will not be opened until blinding has ceased. A well-trained acupuncture practitioner, who has practiced for more than ten years, performs the intervention according to the assignment. Also, the acupuncturist does not participate in any of the subsequent evaluation phases. Investigators, including the study physicians and the analyzing statistician, are blinded to the manipulation group assignment.

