### Measurements of tinnitus

The efficacy of acupuncture treatment for tinnitus is assessed in terms of the severity and loudness of tinnitus. Tinnitus Handicap Inventory (THI) and a 10-cm Visual Analog Scale (VAS) are used. Patients complete the THI and VAS before the treatment and every four weeks during the following period. The 25-item THI consists of three scales: a functional subscale, a catastrophic response subscale and an emotional subscale. Before and after the acupuncture treatment, the participants are asked to report their tinnitus on the THI Questionnaire with ‘Yes’ (4 points), ‘Sometimes’ (2 points) or ‘No’ (0 points). Based on the total THI score, each patient’s tinnitus severity could be categorized into ‘no handicap’ (0 to 16), ‘mild handicap’ (18 to 36), ‘moderate handicap’ (38 to 56) and ‘severe handicap’ (58 to 100).

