### Statistical analysis

We conducted a pilot study, in which the similar outcome measurements were used, to determine the sample size prospectively. In this pilot study, the two methods of manipulation and non-manipulation were about 70 and 50% effective respectively when the patients underwent acupuncture 5 times a week for 4 weeks. Based on the population rates of the two groups, the following formula is used to estimate sample size [16]:

Calculations are performed c 5% significance level. In the formula, α = 0.05, Z_0.05_  = 1.96, β = 0.10, Z_0.10_  = 1.282; n_1_, n_2_ represents the sample size of each group respectively and π_1_ = 0.50, π_2_ = 0.70, π_c_ = (π_1_ + π_2_)/2 = 0.60. Thus as a result, an estimated 146 patients per group should be recruited when allowing for a 15% withdrawal rate.

Statistical analysis will be performed using the statistical software package SPSS 19.0 for windows (SPSS Inc, Chicago, IL, USA). Firstly, the baseline characteristics of the two groups, such as age, weight, duration of tinnitus, THI and VAS scores, will be analyzed by an unpaired *t*-test or paired t tests. Then, the second step is to compare the efficacy of *De Qi* or not in the treatment of tinnitus. The average intensity of *De Qi*, the total number of *De Qi* acupoints of all the treatment sessions, the scores of THI and VAS will be tested for normal distribution. If the data follow normal distribution, a two-sample (independent) *t*-test will be used. The data that are not conforming to the normal distribution will undergo Wilcoxon testing. A level of *P*-value less than 0.05 will be considered statistically significant.

Furthermore, the intention-to-treat analysis (ITT) and per-protocol (PP) analysis should be conducted as two principles to test whether the result of this trial is credible. Any cause of withdrawal or loss to follow-up should be clarified. Qualified statisticians will perform the statistical analysis in a blinded manner.

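### Comparing ITT with PP is the stated test of credibility, but with tests that need an observed score it can miss bias from the planned 15% withdrawal

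*Protocol article*

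**What the plan says.** All references are to the protocol article.

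- **Role of ITT and PP.** Under *Statistical analysis*, the two analyses "should be conducted as two principles to test whether the result of this trial is credible". Neither is given precedence. The abstract (*Methods and design*) presents the same pair as the response to withdrawals: "If any subjects are withdrawn from the trial, intention-to-treat analysis (ITT) and per-protocol (PP) analysis will be performed".
- **Tests.** Under *Statistical analysis*, for the THI and VAS scores: "If the data follow normal distribution, a two-sample (independent) *t*-test will be used". Otherwise a Wilcoxon test is used. No other efficacy test is named.
- **Data collected.** Under *Measurements of tinnitus*: "Patients complete the THI and VAS before the treatment and every four weeks during the following period".
- **Expected loss.** Under *Statistical analysis*: "an estimated 146 patients per group should be recruited when allowing for a 15% withdrawal rate".
- **Other handling of withdrawals.** *Quality control* asks for the reason to be established and the rate to be analysed. *Statistical analysis* repeats that causes of withdrawal or loss to follow-up should be clarified.
- **Grounds for withdrawal.** Under *Withdrawal from the study*, being unable to take full part in treatment or follow-up is one of them.

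**The concern.** A credibility check should be able to fail when the result is wrong. The main threat after randomisation here is loss of patients for reasons tied to their tinnitus. The outcomes are self-rated, and one arm is deliberately given stronger needle sensations, so it is plausible that patients leave for different reasons, or at different rates, in the two arms.

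A t-test or Wilcoxon test at a visit uses only patients with a score at that visit. Without imputation, a patient who has left is absent from the ITT test at that visit as well as from the PP test. The withdrawal rule pushes the two sets closer still, because incomplete participation is itself a ground for withdrawal. What remains different is mainly patients who deviated but still attended. Agreement between the two analyses then says little about those who left. A biased THI or VAS difference could be presented as credible because PP repeats it.

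A single-visit test also leaves out the earlier four-weekly scores of patients who leave later. Those scores carry information about how these patients were doing.

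**Working it through.** **1. The plan's own figure.** Inputs from *Statistical analysis*: 5% two-sided level (Z = 1.96), β = 0.10 (Z = 1.282), rates 0.50 and 0.70, pooled rate 0.60. Allocation is 1:1 (*Recruitment and randomization procedures*).

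n = [1.96·√(2·0.60·0.40) + 1.282·√(0.50·0.50 + 0.70·0.30)]² / 0.20² = 124.04, taken as 124 per group.

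124 / (1 − 0.15) = 145.9, so 146 per group. The figure reproduces. The plan therefore expects about 22 withdrawals per group, or 44 of 292.

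**2. Illustration with no true effect and unequal withdrawal.** The effective-rate scale is used because it is the one the sample size rests on; the same mechanism applies to mean scores. Assumed: 50% effective in both arms, 20% withdrawing in one arm and 10% in the other (15% overall), and every withdrawal a non-responder.

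- Arm losing 20%: 0.50 / 0.80 = 62.5% of completers, n = 0.80 × 146 ≈ 117.
- Arm losing 10%: 0.50 / 0.90 = 55.6% of completers, n = 0.90 × 146 ≈ 131.
- False difference: 6.9 percentage points.
- SE = √(0.625·0.375/117 + 0.556·0.444/131) = 0.0624, so the expected z is 0.0694 / 0.0624 = 1.11.
- Chance of a significant result at the two-sided 5% level: about 20%.

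An ITT analysis restricted to observed patients and a PP analysis of the same completers give the same false difference.

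**3. Equal withdrawal, unequal reasons.** Assumed: 22 of 146 leave each arm, 50% effective in both. Control withdrawals are random, so 62/124 = 50.0% of control completers are effective.

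| Non-responders among manipulation withdrawals | Manipulation completers effective | False difference (points) |
|---|---|---|
| 50% | 62/124 = 50.0% | 0 |
| 75% | 67.5/124 = 54.4% | 4.4 |
| 100% | 73/124 = 58.9% | 8.9 |

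The first row is the case where withdrawal is unrelated to outcome, and there is no bias.

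**4. How far ITT and PP agree when both use observed scores.** Simulation on a continuous score with no true effect: 4,000 trials, 146 per arm, 22 withdrawals per arm. Withdrawal is random in one arm and strongly weighted to poor outcomes in the other. The bias was 0.19 SD in both analyses, and the t-test rejected in about 34% of trials. The two analyses gave the same significance verdict in 100% of trials when the sets were identical, 93.5% when PP dropped a further 5% of attenders at random, and 90.5% when it dropped 10%. The withdrawal pattern and the extra PP exclusions are assumptions, and the agreement figures follow largely from the latter.

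**5. The same case as step 2, with withdrawals kept in ITT as failures.** ITT gives 73/146 = 50% in both arms; PP still gives 62.5% v 55.6%. In simulation ITT rejected in about 5% of trials and PP in about 20%, and ITT supported only 13 to 14% of the false PP positives. The comparison then does react to the bias, but the article does not say which analysis is to be believed.

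**The case against.** The strongest reply is that the article nowhere limits ITT to attended visits. It defines neither set and states no rule for missing scores, and those are details a journal article may leave to the full protocol or analysis plan. Naming a t-test does not rule out imputing first. This stands: that both analyses share the same patients is conditional on no imputation.

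A reader might go further and infer that ITT and PP must agree almost by construction, even with every withdrawal kept in ITT, since they would share 85% of patients. Step 5 refutes that: with withdrawals counted as failures, the two diverge exactly where the bias lies. Nor does the article make agreement a formal pass or fail criterion; that is the natural reading of its sentence, not its wording.

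It is also fair to say that the pair is not the only provision. Reasons for withdrawal must be established and the rate analysed. If rates are compared by arm, which the article does not say, a 20% v 10% imbalance would be significant in about 68% of trials. This helps, but it shows that a problem may exist without showing what it does to the treatment difference. It would also miss the equal-rate case in step 3.

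Finally, the false-positive rates depend on assumed withdrawal patterns. A reader might take 20% or 34% as the error rate of this trial; no figure in the article supports that.

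**Conclusion.** The point holds in a conditional form. The article states a rule: run ITT and PP together to test credibility, with neither named as deciding. With the tests it names, and if missing scores are not imputed, that comparison can miss attrition bias, because both analyses omit largely the same patients. If missing scores are imputed, the two can disagree, and the stated rule gives no verdict.

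Under the assumed patterns the false difference runs from 0 to about 9 percentage points: 6.9 points and about 20% false positives in the main illustration, and 0 when withdrawal is unrelated to outcome. The bias requires that withdrawal be related to outcome and that its rate or its reasons differ by arm. The documents do not show that this will happen, nor that the check must pass when it does. The change is worth making because the plan expects about 44 withdrawals, the better analysis uses scores already scheduled, and it costs little.

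**What to change.** In *Statistical analysis*, with the abstract aligned:

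1. Make ITT, meaning all randomised patients in the arm to which they were randomised, the deciding analysis. State it without the abstract's condition that someone must have withdrawn.
2. Fit it, for THI and likewise for VAS, as a repeated-measures model on all the four-weekly scores, with arm, visit, arm-by-visit and the baseline score. Visits attended before a patient leaves then contribute.
3. Report PP as supportive only, and remove the ITT/PP comparison as the test of credibility.
4. Judge robustness to withdrawals by a sensitivity analysis on the missing scores. For example, multiply impute them, worsen the imputed values by steps that differ by arm (such as 0, 4, 8 and 12 THI points), and report the step at which the conclusion changes.
5. Keep the recording of withdrawal reasons and the analysis of the rate, by arm.

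The cost is wording and a little more programming, with no new patients, visits or data. The downside is that the model assumes scores are missing at random given those observed, which the sensitivity analysis is there to probe.

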## Discussion

Although acupuncture is one of the major parts of TCM, it is regarded as a useful complementary therapy to conventional medicine and the efficacy of acupuncture has been proven by many randomized controlled trials [17–19]. Also, it has been widely believed that the needle sensation is important in acupuncture treatment. In one of our surveys of acupuncture treatment for tinnitus, most of the patients and acupuncturists believed that stronger needle sensations led to better treatment results. However, it is still believed by some researchers that the therapeutic effects of acupuncture are due to the psychological factors [20]. The relationship between *De Qi* and treatment effects is still controversial. Further studies were conducted to explore the relationship among *De Qi*, psychological factors, and clinical efficacy. Xiong *et al*. [21] reported that it was *De Qi*, but not psychological factors, that determined the therapeutic efficacy of acupuncture treatment for primary dysmenorrhea. Kong *et al*. [22] found significant correlations between analgesia and needle sensations of numbness and soreness on experimental pain, which suggested that attributes of *De Qi* sensations might be useful clinical indicators of effective treatment. As for tinnitus, although there was pilot, sham-controlled and double-blind trial to verify the efficacy of the treatment of acupuncture [18], the degree and the type of *De Qi* were not clarified. Further study should be designed to explore the relationship between *De Qi* and acupuncture points, stimulation and treatment effects.

In a recent systematic review of acupuncture for the treatment of tinnitus [23], a total of nine RCTs were included and *De Qi* was considered in six of these trials. In the present data set, no evidence could be found that *De Qi* exerted an important influence on the clinical outcome. However, there are some flaws in the trials that might influence the quantity and quality of the primary data. First, most of the trials had a high risk of bias, such as lack of power calculation, existing of exclusion or attrition bias due to not reporting the dropouts and withdrawals, and insufficient description of randomization, blinding and allocation concealment. Second, although acupuncture points were selected according to TCM theory in the nine studies, constant acupoints were used for all patients except two [24, 25]. It is more rational to select proper points and treat the patients individually based on differentiation of signs and symptoms of tinnitus. Based on the analysis of the previous studies, some improvements have been made in this study and we hope we will be able to reach a reliable evidence of the efficacy of acupuncture for tinnitus and to know the role of *De Qi* in this treatment.

## Trial status

The recruitment of patients will start 1 June 2014, and it is expected that by 31 October 2014 the required sample size will be reached.

## Abbreviations

C-MMASS: The Chinese version of the ‘modified’ Massachusetts General Hospital Acupuncture Sensation Scale
CT: computed tomography
ECG: electrocardiogram
HANDS: the Hospital Anxiety and Depression Scale
ITT: intention-to-treat analysis
TCM: Traditional Chinese Medicine
THI: the Tinnitus Handicap Inventory
PP: per-protocol
VAS: Visual Analog Scales.
